## Abstract

**Background:**

Foot baths are used in complementary and alternative therapy to improve the duration and quality of sleep and reduce tension, anxiety, fatigue, and confusion. They are also known to improve the frequency of labor contractions and to increase their duration in women; thus, they are commonly used by midwives in clinical settings in Japan. However, the physical and mental effects of foot baths during labor are unknown.

**Objective:**

This study aims to assess the physical and mental effects of foot baths based on biomarker levels and self-administered questionnaires.

**Methods:**

A single-arm pre-post test trial design is being used in this study, and the study is being conducted at a general hospital in Tochigi Prefecture, Japan. The target study population is women in the first stage of labor, the phase when the uterus starts to contract and when the cervix dilates to 10 cm, or those undergoing labor induction. Participants who meet the eligibility criteria are recruited, and written informed consent is obtained from them. They are asked to answer the questionnaire and to collect 1.5 mL of saliva in 2 microtubes each, before and after the intervention. The intervention is foot baths for 15-20 minutes using a foot bath device. Data on delivery, such as gestational age, gravidity, parity, diagnosis following the last vaginal examination, and presence or absence of membrane rupture, are retrieved from the medical records. The primary outcomes are salivary cortisol levels before and after the foot baths. The secondary outcomes are levels of relaxation and comfort, labor pain, body warmth, vital signs, and interval of labor pain before and after the foot baths, which are assessed using a numerical rating scale. A paired *t* test or Wilcoxon signed-rank test will be performed to compare the data for salivary cortisol levels and numerical rating scale scores.

**Results:**

Data collection started on April 1, 2022. As of October 2022, we had enrolled 10 participants. Because of the COVID-19 pandemic in Japan, it is difficult for medical personnel to freely interact with women in labor until the results of the COVID-19 polymerase chain reaction test are available in the research facility, complicating the recruitment process.

**Conclusions:**

This is the first prospective study to assess the effects of foot baths using a biomarker during the first stage of labor. The findings on the effects of foot baths on women in labor will provide novel insights that may improve the outcomes of delivery. A randomized controlled trial to investigate the effects of foot baths to obtain robust evidence should be conducted in the future.

**Trial Registration:**

University Hospital Medical Information Network-Clinical Trial Registry UMIN000046539; https://tinyurl.com/2wwj7dns

**International Registered Report Identifier (IRRID):**

DERR1-10.2196/39985

## Introduction

### Background

Foot baths are used for cleaning the feet and are useful in complementary and alternative therapy. Foot baths improve the duration and quality of sleep among postmenopausal and older adults [1-4], decrease low back pain in pregnant women [5], and have psychological effects, such as reduced tension, anxiety, fatigue, and confusion in women [6,7]. They are also known to be effective in decreasing edema of the lower limbs by improving blood circulation due to blood vessel dilation [8].

Studies evaluating the effect of foot baths in the first stage of labor reported that they improve the frequency of labor contractions in women with slow labor [9] and increase the duration of labor contractions in primiparous women [10]. Thus, foot baths may show effects on labor induction.

The epidural labor rate has been increasing in Japan (4.6% in 2014, 5.5% in 2015, and 6.1% in 2016) [11], although it remains lower than that in European or American countries [11-15]. One reason for the low rate of epidural labor in Japan is the low number of anesthetists and obstetricians in the country, affecting their availability for all cases. Therefore, several nonmedical methods are used for labor pain relief in clinical settings, including hot bath therapy, reflexology, aroma therapy, breathing, and massage [15-17]. Although previous studies have reported the psychological and labor-inducing effects of foot baths [6,7,9,10], the sample size of some of these studies was small, and others did not include women in labor. Furthermore, the physical and mental effects of foot baths during labor, such as the effects on relieving labor pain, improving relaxation, or decreasing stress, remain unknown, and no study has investigated the effect of foot baths on women in labor using biomarkers. Cortisol is a hormone secreted by the suprarenal cortex and is widely used as a biomarker to measure stress levels. If foot baths are shown to reduce stress in women in labor, they can be recommended for the nonmedical care of women in labor. Therefore, investigating the physical and mental effects of foot baths on women in labor, especially their pain-relieving effects, can facilitate mental relief and a satisfactory childbirth experience for women in labor. Foot baths are commonly used by midwives in clinical settings in Japan and are expected to have psychological and labor-inducing effects.

### Study Aims

This study aims to investigate the physical and mental effects of foot baths using a biomarker and self-administered questionnaire.

## Methods

### Study Design

We are conducting a single-arm, pre-post test trial to evaluate the effectiveness of foot baths.

### Study Setting and Population

The study is being conducted at a general hospital in Tochigi Prefecture, Japan. The inclusion criteria are women in the first stage of labor or those undergoing labor induction. The first stage of labor is the phase when a pregnant woman’s uterus starts to contract and they feel persistent contractions and relaxation, and the cervix dilates to 10 cm. Women who cannot complete the questionnaire or cannot participate in the study because of labor pain or those who are judged to have difficulty participating in the study by midwives because of low literacy of Japanese or due to mental illnesses are excluded from recruitment.

### Intervention Description

This is a pre-post test trial; therefore, all participants are to receive the intervention. In this study, a foot bath is defined as the immersion of feet up to the ankle in hot water, set to a temperature that feels comfortable to the participants (38 °C to 42 °C) for 15-20 minutes (Figure 1). During the foot bath, other stimuli, such as pushing acupoints or massage, are avoided, because a meta-analysis has shown the effects of acupressure on labor duration [18]; this point was explained to all research assistants before starting this study. Participants receive the foot bath intervention only once, because midwives usually provide foot baths for women in labor only once in clinical settings; therefore, we aim to evaluate the effects of a single foot bath intervention. The intervention is discontinued if delivery progresses rapidly and if the midwives consider it difficult to continue.

**Figure 1 figure1:**
[figure not shown]
Protocol of the study.

### Data Collection

#### Variables

Data collection is being undertaken by research assistants, who are midwives working in the hospital and on duty, as assigned by the midwife in charge.

Data are collected using a self-administered questionnaire, laboratory assay for the biomarker, anthropometric measurements, and medical records. The self-administered questionnaire was adapted from those developed in previous studies that assessed the effects of foot baths [7,19-23]. Participants are asked to answer a questionnaire evaluating sociodemographic data, such as age, marital status (married, single, divorced, or widowed), education level (junior high or high school; vocational school, junior college, or technical college; and university or graduate school), and occupation (employee, public servant, self-employed, part-time worker, unemployed or housewife, and others). Previous studies used a 10 cm ruler to assess the comfort or feeling of body warmth [19,24], with 0 cm meaning “not at all” and 10 cm meaning “extremely so”; thus, in this study, a numerical rating scale (NRS), ranging from 0 to 10, is being used to collect data on the levels of labor pain and comfort, relaxation, and degree of warmth of the legs and entire body. Participants are asked to provide 1.5 mL of saliva in 2 microtubes before and after the foot bath. Vital signs, such as blood pressure, body temperature, pulse rate, and respiratory rate, are measured by research assistants before and after the foot bath. Data on delivery (gestational age, gravidity, parity, diagnosis following the last vaginal examination [such as dilation, station, effacement, consistency, and position], presence or absence of membrane rupture, use of uterine contraction agents, and estimated fetal body weight) are retrieved from the medical records by the research assistants and entered in the questionnaire.

The primary outcome of this study is salivary cortisol levels before and after the foot bath. The secondary outcomes are levels of labor pain, comfort and relaxation, and leg and body warmth, assessed using NRS scores, vital signs, and intervals of labor pain before and after the foot bath.

#### Data Collection Methods

We asked some experienced midwives working at the hospital to assist in this study as research assistants. Before study initiation, instructions on data collection and intervention were provided and explained to the research assistants.

The research assistants recruit participants for the study and explain the purpose and contents of the study using an instruction sheet. After obtaining oral consent, written informed consent is obtained.

The research assistants provide the participants with the self-administered questionnaire along with a clipboard and pen. Participants are asked to complete the self-administered questionnaire. After completion, the midwives measure the participants’ vital signs (blood pressure, body temperature, pulse rate, and respiratory rate) and the interval and duration of labor pain.

They also request participants to provide 1.5 mL of saliva in 2 microtubes each. After saliva collection, the specimens are stored at −20 °C until analysis.

The research assistants provide foot baths to participants using a foot bath device (Hietori-kun Micon Premium, FB-C80, Koyo Co, Ltd, Gifu, Japan). The temperature of the water is set to 38 °C to 42 °C, as desired by the participants. AS mentioned, during the foot bath, the research assistants avoid applying pressure on acupoints. The participants are allowed to soak their feet in the bath quietly for 15-20 minutes.

After the foot bath, the research assistants provide the participants with a self-administered questionnaire with a clipboard and pen. After completing the questionnaire, they measure the vital signs (blood pressure, body temperature, pulse rate, and respiratory rate) and the interval and duration of labor pain.

After saliva collection, the specimens are stored at −20 °C until analysis. If the participants have difficulty providing saliva because of severe labor pain, only responding to the self-administered questionnaire and the measurement of the vital signs is allowed.

After recruitment, all salivary cortisol level measurements are conducted at Yanaihara Institute Inc, Shizuoka, Japan.

We will continue to recruit participants until the target sample size is attained, and we may consider adding another hospital as a study setting in case the recruitment does not progress favorably because of the COVID-19 pandemic. It is difficult for medical personnel to freely interact with women in labor until the results of the COVID-19 polymerase chain reaction test are available, complicating the recruitment process.

Data are double-checked during entry, and the data ranges are checked to ensure data quality. The collected data and questionnaires are stored in a locked cupboard.

### Sample Size Calculation

According to a previous study that investigated differences in salivary cortisol levels before and after foot baths [20], the sample size was calculated based on the following considerations: effect size (Cohen *d*)=0.4, α (2-tailed)=.05, and *β*=.80. We estimated the sample size using a two-tailed *t* test to be equal to 100.

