### Data Analysis

Categorical variables, such as marital status, education level, and occupation, will be presented as n (%), and continuous variables (salivary cortisol levels; NRS scores for labor pain, comfort, and relaxation; and vital signs, such as blood pressure, body temperature, pulse rate, and respiratory rate) will be presented as mean (SD) if normally distributed or as medians and interquartile ranges if nonnormally distributed. We will perform paired *t* tests for continuous variables if the observations are normally distributed, and if they are not, we will perform the Wilcoxon signed-rank test to compare data before and after foot baths. Furthermore, we will divide the participants into 2 groups, nullipara and multipara, for sensitivity analysis. All missing pretest or posttest data for the main outcome will be excluded from the analysis.

All data will be analyzed using SPSS Statistics for Windows (version 28.0; IBM Corp). Two-tailed *P* values of <.05 will be considered statistically significant.

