## Results

Data collection started on April 1, 2022. As of October 2022, we had enrolled 10 participants. Because of the COVID-19 pandemic in Japan, it is difficult for medical personnel to freely interact with women in labor until the results of the COVID-19 polymerase chain reaction test are available in the research facility, complicating the recruitment process. Moreover, the number of medical personnel who can engage in the research decreased in the research facility because some staff were infected by COVID-19; thus, recruitment is currently not progressing.

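### The stated effect size, power and sample size of 100 do not fit the planned paired analysis, and β is mislabelled

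*Protocol article*

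**What the plan says.** The design is a single group measured twice: "We are conducting a single-arm, pre-post test trial to evaluate the effectiveness of foot baths" (Study Design). Data Analysis specifies the comparison: "We will perform paired *t* tests for continuous variables if the observations are normally distributed", with the Wilcoxon signed-rank test otherwise. The abstract says the same for the primary outcome: a paired t "test or Wilcoxon signed-rank test will be performed to compare the data for salivary cortisol levels". Significance is two-sided: "Two-tailed *P* values of <.05 will be considered statistically significant".

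The Sample Size Calculation section refers to an earlier study of salivary cortisol before and after foot baths. It lists "effect size (Cohen *d*)=0.4, α (2-tailed)=.05, and *β*=.80" and ends with "We estimated the sample size using a two-tailed *t* test to be equal to 100". It does not say whether that t test is paired or independent, or which SD standardises d. It gives no pre-post correlation, no allowance for missing saliva and no adjustment for the Wilcoxon test.

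The figure governs recruitment: "We will continue to recruit participants until the target sample size is attained" (Data Collection Methods). On progress, the Results section reports: "As of October 2022, we had enrolled 10 participants".

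**The concern.** A sample size statement should let a reader get from the inputs to N using the test that will be run. Here the direct reading, a paired t test with d on the within-woman differences, gives about half the printed number. The printed number is instead what a two-group comparison would need in each group, and this trial has no second group.

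Separately, β is the type II error rate. A value of .80 would mean 20% power.

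At stake is whether the target means what readers will take it to mean. The trial intends to recruit until it reaches 100, and the authors are considering a second hospital to get there. That decision should rest on a correct statement of what 100 women provide.

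**Working it through.** **Inputs.** d = 0.4, two-sided α = .05, and .80 read as power (all from Sample Size Calculation). One group measured before and after (Study Design). Paired t test (Data Analysis). Power is from the noncentral t distribution, with the normal approximation as a check.

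**1. Which calculation gives 100?** Independent two-sample t test, per group:
- Normal approximation: n = 2 × ((1.960 + 0.842)/0.4)² = 2 × 49.1 = 98.1, so 99.
- Noncentral t: n = 99.08, so 100 per group (200 in total). Power is 79.97% at 99 per group and 80.4% at 100.

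This matches the printed figure, but as a per-group number.

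**2. The planned paired t test, with d = mean change / SD of change:**
- Normal approximation: n = ((1.960 + 0.842)/0.4)² = 49.1, so 50.
- Noncentral t: n = 51.01, so 52 pairs (power 80.8%).
- At 100 pairs, power for d = 0.4 is 97.7%, and 80% power is reached at d = 0.283.

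**3. If d is instead in raw-SD units.** With equal SDs and pre-post correlation r, the effect on the differences is d_z = d/√(2(1-r)).

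| r | d_z | pairs for 80% power | power with 52 pairs | power with 100 pairs |
|---|---|---|---|---|
| 0 | 0.283 | 101 (100.05 before rounding up) | 52% | 79.98% |
| 0.2 | 0.316 | 81 | 61% | 87.9% |
| 0.5 | 0.400 | 52 | 80.8% | 97.7% |
| 0.7 | 0.516 | 32 | 95.5% | 99.9% |

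On this reading 100 arises only at r = 0, which amounts to ignoring the pairing.

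**4. Other routes from 52 to 100** (paired, d on the differences):
- 90% power needs 68 pairs and 95% needs 84. The stated value is .80.
- Wilcoxon signed-rank: 52/0.955 gives 55 and 52/0.864 gives 61 (relative efficiency under normality, and its lower bound).
- Missing pairs: 52/(1-m) = 100 requires m = 48%. No allowance is stated.

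**5. β = .80 taken literally.** Power of 20% would need about 10 pairs (n = 9.74), or 17 per group in a two-sample design (n = 16.53). Neither is near 100, so power = .80 must be meant.

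**The case against.** The strongest reply has three parts.

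**The cause is not documented.** The article says only that a two-tailed t test was used. A reader might infer that the authors applied the two-sample formula. The match is exact, but a paired calculation with a raw-SD d and zero correlation lands within one woman of the same number. The origin therefore remains an inference. This part stands. What does not depend on it is that 100 fails to follow from d = 0.4 on the differences, and that the raw-SD route needs an assumption the article never states.

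**52 is not established as the right target.** A reader might conclude that the trial needs only 52 women. That holds if d is on the SD of change, or on the raw SD with r = 0.5. The article does not give the standardiser and the source study is not at hand. If d is in raw-SD units and r = 0.2, 52 pairs give only 61% power. Women may skip saliva collection (Data Collection Methods), incomplete pairs are excluded, and a Wilcoxon test may replace the t test (Data Analysis), so a margin above 52 is useful. This part also stands.

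**The error is in the safe direction.** On the differences reading, 100 pairs give 97.7% power and even 80 complete pairs give 94.2%. The type I error rate and the estimate are unaffected. This is correct, and it limits the consequence.

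A reader might also blame the target for the slow recruitment. The Results section attributes the delay to pandemic access limits and staff infections. Progress under those conditions is no basis for projecting when recruitment would finish.

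**Conclusion.** The point holds as an inconsistency between the printed inputs, the printed N and the planned test. With d = 0.4 on the SD of change, two-sided α = .05 and 80% power, the paired t test needs 52 complete pairs. The stated 100 gives 97.7% power, or 80% power at d = 0.283. Those figures rest on the standardiser being the SD of change. If it is the raw SD, the requirement runs from 101 pairs at r = 0 to 32 at r = 0.7, and only zero correlation supports 100.

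The trial is not underpowered on its stated inputs. The β label is a separate notation slip that does not affect these numbers.

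**What to change.** Rewrite the Sample Size Calculation paragraph so that it:

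1. names the paired t test as the basis of the calculation;
2. states, from the source study, whether d = 0.4 is on the SD of change or on the raw SD, and in the latter case the assumed pre-post correlation;
3. replaces the β entry with power (1-β) = .80, that is β = .20;
4. keeps 100 and says what it delivers: with d on the differences, 100 complete pairs give 97.7% power at d = 0.4, or 80% power at d = 0.28.

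Lowering the target is defensible only after the source study's d is confirmed to be on the SD of change. It should then start from about 55 to 61 pairs to cover the Wilcoxon alternative, with a stated allowance for missing saliva on top. As an illustration only, assuming 10% to 20% of pairs are incomplete, 55/0.9 gives 62 enrolled and 61/0.8 gives 77.

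The cost is one corrected paragraph and a check of the source study. No additional participants are needed.

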### Patient and Public Involvement

Neither patients nor the public are involved in the design, conduct, reporting, or dissemination of the study.

### Data Analysis

Categorical variables, such as marital status, education level, and occupation, will be presented as n (%), and continuous variables (salivary cortisol levels; NRS scores for labor pain, comfort, and relaxation; and vital signs, such as blood pressure, body temperature, pulse rate, and respiratory rate) will be presented as mean (SD) if normally distributed or as medians and interquartile ranges if nonnormally distributed. We will perform paired *t* tests for continuous variables if the observations are normally distributed, and if they are not, we will perform the Wilcoxon signed-rank test to compare data before and after foot baths. Furthermore, we will divide the participants into 2 groups, nullipara and multipara, for sensitivity analysis. All missing pretest or posttest data for the main outcome will be excluded from the analysis.

All data will be analyzed using SPSS Statistics for Windows (version 28.0; IBM Corp). Two-tailed *P* values of <.05 will be considered statistically significant.

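### Dropping women without both saliva samples, when severe labor pain is the stated reason for skipping saliva, may bias the primary cortisol change, plausibly toward an apparent reduction

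*Protocol article*

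**What the plan says.** The Variables section defines the endpoint: "The primary outcome of this study is salivary cortisol levels before and after the foot bath". The Data Analysis section plans a paired t test, or a Wilcoxon signed-rank test if the data are not normal, and fixes the handling of incomplete pairs: "All missing pretest or posttest data for the main outcome will be excluded from the analysis". The one sensitivity analysis named there is a split into nulliparous and multiparous women.

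The Data Collection Methods section gives one reason why a sample may be absent, and a reduced set of measurements for such women: "If the participants have difficulty providing saliva because of severe labor pain, only responding to the self-administered questionnaire and the measurement of the vital signs". The sentence comes after the description of the post-bath steps. The women it covers therefore still provide NRS scores for labor pain, comfort, relaxation and warmth, and their vital signs.

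Two neighboring rules bear on the point. At recruitment, the Study Setting and Population section excludes "Women who cannot complete the questionnaire or cannot participate in the study because of labor pain". During the bath, the Intervention Description section says: "The intervention is discontinued if delivery progresses rapidly and if the midwives consider it difficult to continue".

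**The concern.** An unadjusted paired test on complete pairs estimates the mean change for all treated women only if the loss of a sample is unrelated to that change. Here the protocol itself ties the loss to severe labor pain. Pain is a secondary outcome, and cortisol is measured as a marker of stress. If women whose pain and cortisol rose during the bath are the ones who give no post-bath sample, the remaining women look more favorable than the treated group as a whole.

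The trial has one arm, so no comparator shares the loss and any selection goes straight into the effect estimate. The Conclusion section says foot baths can be recommended if they are shown to reduce stress, so a spurious reduction would have consequences. The pain scores that could inform the missing values are collected, but the primary analysis makes no use of them.

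**Working it through.** **The plan's own figures.** The protocol gives no missing rate, no allowance for missing samples and no relation between pain and cortisol. The only figure to reproduce is the sample size of 100 (d = 0.4, two-sided α 0.05, the stated β of .80 read as power). An independent two-sample t test needs 99.08, hence 100 per group, which matches. The planned paired t test needs 51.01, hence 52 pairs. Taking d = 0.4 in SDs of the change, the paired test has 97.7% power with 100 pairs, 94.2% with 80 and 91.0% with 70. Lost samples are thus a question of bias here, not of power.

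**Bias model (all inputs assumed).** Let the true mean change be zero and the change have SD 1. Let m be the share of women without a post-bath sample, exactly those with the highest pain, and ρ the correlation of pain with cortisol change. With z = Φ⁻¹(1 − m), the complete-case bias is

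bias = −ρ · φ(z) / (1 − m)

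| m | z | φ(z)/(1 − m) | ρ = 0.3 | ρ = 0.5 |
|---|---|---|---|---|
| 5% | 1.645 | 0.1031/0.95 = 0.109 | -0.03 | -0.05 |
| 10% | 1.282 | 0.1755/0.90 = 0.195 | -0.06 | -0.10 |
| 20% | 0.842 | 0.2800/0.80 = 0.350 | -0.105 | -0.175 |
| 30% | 0.524 | 0.3477/0.70 = 0.497 | -0.15 | -0.25 |

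With 100 women enrolled and 100(1 − m) pairs analyzed, the noncentral t (allowing for the reduced variance after truncation) gives these chances of a significant result when nothing has changed, against a nominal 5%: 6 to 8% at m = 5%, 9 to 16% at 10%, 16 to 37% at 20% and 24 to 59% at 30%.

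**How far this depends on the assumptions.**
- *Ordering by pain.* If the chance of a missing sample rises with pain only probabilistically (logistic, odds ratio 2.7 per SD of pain, 20% missing), the bias is about -0.05 (ρ = 0.3) to -0.09 (ρ = 0.5). That is half the value under perfect ordering.
- *Correlation.* ρ = 0 gives no bias. ρ = -0.3 gives the same size as ρ = 0.3 with the opposite sign (+0.06 at 10%, +0.15 at 30%).
- *What drives the loss.* Suppose the 10 to 20% of women with the highest post-bath cortisol are lost, with a pre-post correlation of 0.5 to 0.7. The bias is then -0.08 to -0.17. If the women with the highest pre-bath cortisol are lost instead, it is +0.08 to +0.17, an apparent increase.

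**The case against.** The strongest reply is that severe pain is a level, whereas the endpoint is a within-woman change. A woman in severe pain before and after the bath may have high cortisol both times and little change, and dropping her does little harm. This stands as a limit on direction and size. A reader might infer that the rule certainly favors the foot bath, but the documents give no relation between pain and cortisol change. Loss driven by high pre-bath cortisol would push the other way. That the waiver concerns mainly the post-bath sample is the natural reading of where the sentence sits, but it is still a reading.

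A reader might also take stopping the bath for rapid progress as a second cause of missing cortisol. The Intervention Description section says only that the bath stops. It does not say that the post-bath sample is then omitted or the woman excluded, so the protocol names one cause, not two.

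The recruitment screen already removes some women in too much pain to take part, which should lower later pain-related loss. Missing rates of 10 to 30% have no basis in the documents. The false-positive rates above are what perfect ordering would produce, not a forecast.

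Finally, sensitivity analyses are often left to a full protocol or analysis plan that is not shown, and the article already says that a single-arm design makes effects hard to judge. Both are fair. But the exclusion rule is stated, not left open, and it sits beside a stated pain-related waiver. The limitations cover the design, the single prefecture and slow recruitment, but not selective loss of saliva.

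**Conclusion.** The concern holds in a limited form. The protocol fixes complete-case analysis for its primary outcome and names severe labor pain as a reason for missing saliva, so missingness is plausibly informative and the primary change may be biased. An apparent reduction is the more plausible direction, provided that the post-bath sample is the one lost and that cortisol rose with pain in those women.

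The size cannot be derived from the documents. For a given missing share and a correlation of 0.3 to 0.5, perfect ordering by pain gives an illustrative upper bound: about -0.06 to -0.10 SD at 10% missing and -0.15 to -0.25 SD at 30%. Against the target of 0.4 SD, that is roughly 15 to 25% (0.06/0.4 and 0.10/0.4) and 38 to 63% (0.15/0.4 and 0.25/0.4) of the effect sought. Looser ordering or fewer than 10% missing makes it smaller. The change is worth making; confidence is moderate.

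**What to change.** Replace the bare exclusion with an analysis of mean cortisol change in all women who have at least one saliva sample, using multiple imputation. Include in the imputation model the pre- and post-bath NRS pain and relaxation scores, vital signs, parity and cervical dilation. Keep the complete-case paired test as a sensitivity analysis. Add one delta analysis that shifts the imputed values away from missing at random, so that readers can see how large a departure would change the conclusion. Report the number of missing pre- and post-bath samples with the reason for each, and compare pain scores between women with and without saliva.

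The cost is a few sentences in the Data Analysis section and modest programming. All the variables are already collected. The imputation assumes that values are missing at random given pain and the other variables, which the data cannot confirm; the delta analysis probes it. With 10 women enrolled by October 2022, the change could, on the article's account, be specified before most of the data exist.
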